## Outcome evaluation

4

### Primary outcome

4.1

6-month PFS rate: the proportion of all randomized participants who are free of disease progression (assessed per iRECIST criteria) and free from all-cause death at the 6-month time-point from randomization.

### Secondary outcome

4.2

Progression-free survival (PFS), from the start of randomization to the time when the tumor progresses.

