### Recruitment

2.3

The 56 cases in this study were all from advanced lung cancer patients who received immunotherapy at Shanghai TCM-Intergrated Hospital Shanghai University of Traditional Chinese Medicine. All subjects participating in this trial shall provide written informed consent prior to enrollment. The trial workflow is illustrated in **Figure 1**. Subject recruitment remains ongoing as of the date of submission. The first subject was enrolled on June 25, 2026, and the trial is projected to conclude in October 2027.

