Patient performance status score (ECOG score): It was determined according to the ECOG performance status score standard. The ECOG score of enrolled patients was 0–2 points.

Efficacy assessment (RESIST1.1 criteria)

1. Tumor response assessment was performed simultaneously with RECIST 1.1 and iRECIST; preset imaging scanning time points: baseline, every 6 weeks, end of treatment, and follow-up period;2. Set up a centralized image review at a third-party center, with two blinded radiology experts independently reviewing the images, and the differences will be decided by a third expert;3. The rules for handling pseudo-progression are predefined: When immune-related pseudo-progression is suspected, confirmation imaging review will be performed 4–8 weeks later; iUPD will not be judged as PD under the iRECIST criteria, and subjects will continue to be allowed to continue the trial medication; disease progression will be judged only if iCPD is confirmed.

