### Subject follow-up

4.9

The main forms of follow-up are telephone follow-up and outpatient follow-up. Patients are instructed to follow up one week after discharge. If the patient does not go to the outpatient follow-up, telephone follow-up will be changed to once every 3 months, and call records will be made. The survival period is calculated from the day of the first immunotherapy administration to the time of death recorded in the medical record or the patient’s death. The difference between the two times is the survival period; the last follow-up time for surviving patients and patients lost to follow-up is recorded as the censored time, and the survival time is expressed in months. The project conducted the last telephone follow-up visit for all enrolled patients as of the first 3 months.

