### Statistical analysis plan

4.10

Data processing was carried out with SPSS26.0 statistical software. The measurement data gives the mean, standard deviation, minimum, maximum, median, etc., which are expressed as mean ± standard deviation; the counting data gives the frequency distribution and corresponding percentages. T-test was used to compare data groups with normal distribution measurement data; rank-sum test was used for non-normal distribution measurement data, chi-square test was used for counting data, qualitative variables and correlation. Log-rank test was used for survival time and survival rate after treatment. Survival analysis was carried out using Kaplan-Meier method. Using α=0.05 as the test criterion, P<0.05 as the difference is statistically significant.

Information on the start and end times and treatment courses of antibiotics, proton pump inhibitors (PPIs), and probiotics during the trial will be collected, and key dietary covariates will be collected; subjects will not be forced to withdraw from the study due to the use of the above drugs. The preset sensitivity analysis included: excluding subjects who used antibiotics during follow-up; incorporating PPI, probiotics and dietary covariates into the model for correction to evaluate the robustness of the primary endpoint and microbiome and metabolome analysis results.

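### Secondary PFS ends at tumour progression and omits death, so it can disagree with the primary 6-month PFS rate, which counts death from the same origin

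*Protocol article*

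**What the plan says.** Section 4.1 (Primary outcome) takes all randomised participants and counts those without iRECIST progression who are also "free from all-cause death at the 6-month time-point from randomization". Section 4.2 (Secondary outcome) lists one endpoint, progression-free survival, measured "from the start of randomization to the time when the tumor progresses". No other section adds death to it.

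The tumour assessment rules in section 4.3 set a confirmation scan 4 to 8 weeks after suspected pseudo-progression and state that "disease progression will be judged only if iCPD is confirmed".

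Section 4.9 (Subject follow-up) defines a further time measure: "The survival period is calculated from the day of the first immunotherapy administration to the time of death recorded in the medical record". Its censoring sentence reads "the last follow-up time for surviving patients and patients lost to follow-up is recorded as the censored time". Section 4.10 specifies Kaplan-Meier estimation and says "Log-rank test was used for survival time and survival rate after treatment". Survival has a row in Table 2 but is not among the endpoints in sections 4.1 to 4.3.

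**The concern.** Two adjacent sections use the name PFS for different things. The primary is a true progression-free survival proportion. The secondary, taken literally, is time to progression. The two share a start date and differ only in whether death counts.

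The trial population makes the difference more than formal. Entry allows stage IIIB-IV disease, ECOG up to 2 and an expected survival of as little as 3 months, and progression after a suspected pseudo-progression waits for a confirmation scan. A patient who dies in that interval is a failure for the primary endpoint and has no event under section 4.2. The trial could then report two different 6-month PFS figures for the same 56 patients, with the more favourable one coming from the secondary curve. Such deaths are also unlikely to be unrelated to the risk of progression, so the secondary curve would be hard to interpret in its own right.

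The survival period raises a smaller question of the same kind: its clock starts at an event that is not randomisation.

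**Working it through.** **The plan's own figure.** Section 2.2 uses rates of 50% and 10%, with normal quantiles 1.96 and 1.282. Its formula gives (0.5 × 0.5 + 0.1 × 0.9) / (0.4)² × (1.96 + 1.282)² = 0.34 / 0.16 × 10.51 = 22.3, so 23 per group. Then 23 × 1.2 = 27.6, so 28 per group and 56 in total. The figure is reproduced. It rests on a comparison of two proportions and uses nothing from section 4.2.

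**The definitions side by side.**

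| Measure | Starts at | Ends at |
|---|---|---|
| Primary 6-month PFS rate (4.1) | Randomisation | Progression (iRECIST) or death from any cause |
| Secondary PFS (4.2) | Randomisation | Tumour progression only |
| Survival period (4.9) | First immunotherapy dose | Death |

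**Direction.** Let H be the cumulative hazard of progression or death to 6 months, split into progression first (Hp) and death without progression (Hd). True PFS is exp(−Hp − Hd). If deaths without progression are censored, Kaplan-Meier estimates exp(−Hp). This is larger whenever Hd is above zero, whatever the shape of the hazards.

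**Size, as an illustration.** Assumptions, none of them given in the article: constant hazards; a share f of events that are deaths without confirmed progression, from 5% to 30%; and the planning rates of 50% and 10% read as true 6-month PFS. Then Hp = (1 − f) × H, and the secondary curve reads S^(1 − f), where S is the true rate.

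| f | True 50% reads | True 10% reads |
|---|---|---|
| 5% | 0.5^0.95 = 51.8% | 0.1^0.95 = 11.2% |
| 10% | 0.5^0.90 = 53.6% | 0.1^0.90 = 12.6% |
| 20% | 0.5^0.80 = 57.4% | 0.1^0.80 = 15.8% |
| 30% | 0.5^0.70 = 61.6% | 0.1^0.70 = 20.0% |

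If patients who died were instead carried forward as not progressed, the reading would be 1 − (1 − f)(1 − S). That gives 52.5% to 65% for a true 50%, and 14.5% to 37% for a true 10%. The direction is the same and the gap is larger.

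**Between arms.** With the same f in both arms, the factor (1 − f) cancels from the ratio of the hazards, so the hazard ratio does not move; what changes is the level of each curve and the number of events. The comparison itself shifts only if the share differs by arm, on which the article says nothing.

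**Survival origin.** Section 3.2 asks that patients be willing to receive immunotherapy, while section 2.3 describes "advanced lung cancer patients who received immunotherapy at" the centre. Neither fixes the first dose relative to randomisation. A first dose after randomisation drops early follow-up, and a randomised patient who is never dosed has no start date.

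**The case against.** The strongest reply is that section 4.2 is loose shorthand. The endpoint is named progression-free survival, the section directly above counts all-cause death, and nothing tells the analyst to censor deaths. That is fair as to intent. It does not change the text, which states an end point for the clock and leaves death out. A reader might infer that the plan orders deaths to be censored. It does not: the only censoring sentence belongs to the survival period and covers survivors and patients lost to follow-up. Censoring at death is the ordinary consequence of the definition, not a stated rule. The absence of a detailed PFS censoring rule is no fault either, since that is commonly left to the SAP.

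Other stronger readings also go too far:

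- Secondary PFS does not have a different time origin. It starts at randomisation, as the primary does.
- The survival period is not wrong to end at death. It is overall survival in effect, and only its origin is in question.
- One might infer that patients already on a checkpoint inhibitor gain time in which they could not have died in the trial. Section 2.3's past tense is weak support, because the article describes planned steps in the past tense elsewhere. Section 3.2 looks forward, and section 3.3 excludes people who have had other immune-related therapies, although that wording is ambiguous. Time before randomisation also cannot depend on the allocated arm, so it would not systematically favour either group.
- No count of lost events can be given. The article states neither an expected number of PFS events nor a share of deaths without progression.

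**Conclusion.** The concern stands for the event definition. Section 4.2 as written is time to progression under the PFS name and conflicts with section 4.1 on whether death counts. The direction is certain if any patient dies without confirmed progression before 6 months and is censored: the secondary curve at 6 months lies above the primary rate. The size is unknown. The illustrated excess is about 2 to 12 percentage points on a true 50% and 1 to 10 on a true 10%, and it rests wholly on the assumed 5% to 30% share and constant hazards.

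The survival origin is a lesser point. It matters only if survival is compared between arms, and survival is not a listed endpoint.

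This is a definition worth correcting, not a threat to the trial's main conclusion. The primary endpoint is properly defined in all randomised participants, and the sample size does not depend on the secondary endpoint.

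**What to change.** Reword section 4.2 so that PFS is the time from randomisation to first progression, judged and dated by the same iRECIST rule as the primary endpoint, or death from any cause, whichever comes first. The censoring details can sit in the SAP.

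In section 4.9, if survival is to be compared between arms, measure it from randomisation to death from any cause in all randomised patients. Time from the first immunotherapy dose may be kept as a description.

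The cost is two sentences. Randomisation dates, scans and survival follow-up are already part of the schedule, so no new visits or patients are needed. Recruitment is still open and formal unblinding follows database lock, so the change can be made without knowledge of results, preferably before the planned interim analysis.

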### Exploratory study endpoints

4.3

Including TCM syndrome integral, EORTC QLQ-C30, ECOG score, intestinal barrier, intestinal flora, inflammatory cytokines, T cell subsets, etc.

TCM syndrome integral: TCM syndrome integral record time refer to evaluation time point in **Table 2**.

TCM Syndrome Points:

The severity of primary symptoms and secondary symptoms was divided into 0, I, II and III according to the single scoring standard of primary symptoms and secondary symptoms. Grade 0: asymptomatic, 0 points; Grade I: mild symptoms, not affecting daily life and work, 1 point; Grade II: moderate symptoms, partially affecting daily life and work, 2 points; Grade III: severe symptoms, affecting daily life, difficult to persist in work, 3 points.

The evaluation of syndrome efficacy includes changes in main symptoms, secondary symptoms, signs, and tongue images. It is calculated using nimodipine method. The efficacy index = [(pre-treatment points subtract post-treatment points)/pre-treatment points]×100%, which is divided into 4 levels: clinical recovery, effective, and ineffective.

1. Clinical recovery: The main symptoms, secondary symptoms, and signs disappeared or basically disappeared, the tongue picture basically returned to normal, and the efficacy index was ≥95%;2. Effective effect: The main symptoms, secondary symptoms, signs, and tongue symptoms have been significantly improved, with 70%≤ efficacy index <95%;3. Effective: The main symptoms, secondary symptoms, signs, and tongue symptoms have improved, 30%≤ efficacy index<70%;4. Ineffectiveness: The main symptoms, secondary symptoms, signs, and tongue manifestations have not been significantly improved or even worsened, and the efficacy index is<30%.

Quality of life QOL score and weight monitoring: application of EORTC QLQ-C30 scale.

A standardized PRO management and compliance monitoring plan is preset for the study: questionnaires are filled out independently at baseline, every 2 treatment cycles, and on site at the end of treatment. The investigators only provide process answer questions and do not induce answers. The questionnaire completion rate, missing item rate and compliance were monitored throughout the process; cases with low compliance were recorded, and the robustness of the results was verified through sensitivity analysis.

Patient performance status score (ECOG score): It was determined according to the ECOG performance status score standard. The ECOG score of enrolled patients was 0–2 points.

Efficacy assessment (RESIST1.1 criteria)

1. Tumor response assessment was performed simultaneously with RECIST 1.1 and iRECIST; preset imaging scanning time points: baseline, every 6 weeks, end of treatment, and follow-up period;2. Set up a centralized image review at a third-party center, with two blinded radiology experts independently reviewing the images, and the differences will be decided by a third expert;3. The rules for handling pseudo-progression are predefined: When immune-related pseudo-progression is suspected, confirmation imaging review will be performed 4–8 weeks later; iUPD will not be judged as PD under the iRECIST criteria, and subjects will continue to be allowed to continue the trial medication; disease progression will be judged only if iCPD is confirmed.

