### Drop-out criteria

3.5

Abnormal function of important organs of the subject during the clinical trial;The subject experienced severe drug allergic reactions during the clinical trial;Serious adverse reactions require discontinuation of trial drug treatment;Patients cannot tolerate adverse drug reactions;Poor patient compliance during the clinical study affects the effectiveness and safety evaluation, and subjects cannot be completed.

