### Intervention method

3.8

Treatment group: Jianpi Guchang granules, 1 bag each time, twice a day. Combined with immunotherapy (a. Define and stratify according to PD-L1 tumor proportion score and EGFR/ALK/KRAS/BRAF status, driver gene negative, any PD-L1 level: platinum-containing chemotherapy combined with immunotherapy is an important first-line option. When PD-L1 TPS>1% subjects, combined PD-1/PD-L1 immunotherapy is allowed. b. Choose a chemotherapy regimen that complies with guideline recommendations). There is a course of treatment every 21 days, and there are a total of 4 courses of treatment.Control group: The control group received oral granules at 1/10 of the original dose of the treatment group, and other treatment options were the same as those in the treatment group. Every 21 days is a course of treatment, and a total of 4 courses of treatment are provided.

Granules:The granules and placebo used in the trial were produced by Shanghai Wanshicheng Pharmaceutical Co., Ltd.

**Table 2** presents the timeline for subject screening, trial interventions and study assessments.

**Table 2 T2:** Trial timeline.

Visit	Screening	Drug intervention period (weeks)				After drug withdrawal	Further follow-up (Every three months until 3 months before the end of the project or the patient's death)
	0d	3	6	9	12	3 months	
Informed consent form	×						
Demographic information	×						
Inclusion and exclusion criteria	×						
General information	×						
Vital signs	×						
History of NSCLC and its treatment	×						
History of other diseases and their treatments	×						
TCM syndrome score	×	×	×	×	×		
ECOG score	×	×	×	×	×		
EORTC QLQ-C30	×	×	×	×	×		
Routine blood tests	×		×		×		
Liver function	×		×		×		
Renal function	×		×		×		
Serum and stool samples collection	×		×		×		
Intestinal barrier function	×		×		×		
Gut flora	×		×		×		
Inflammatory cytokines	×		×		×		
T cell subsets	×		×		×		
Imaging evaluation (RESIST1.1)	×		×		×	×	×
Adverse events		×	×	×	×	×	×
Release drugs/placebo	×	×	×	×			
Retrieve empty packages		×	×	×	×		
Drug combination	×	×	×	×	×	×	×
Survival					×	×	×

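### The primary endpoint is fixed at 6 months from randomisation, but the scan that informs it is timed from drug withdrawal, so month-6 status is read at times that depend on when study drug stops

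*Protocol article*

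**What the plan says.** Section 4.1 of the protocol article defines the 6-month PFS rate as the proportion of all randomised participants without progression and "free from all-cause death at the 6-month time-point from randomization". The clock therefore starts at randomisation.

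Table 2 in section 3.8 marks imaging at screening, week 6 and week 12. It then marks one visit at 3 months in the column headed "After drug withdrawal", and further visits "Every three months until 3 months before the end of the project" or death. Section 3.8 sets the treatment length: "There is a course of treatment every 21 days, and there are a total of 4 courses of treatment".

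Section 4.3 describes the scans as "preset imaging scanning time points: baseline, every 6 weeks, end of treatment, and follow-up period". It gives neither an interval nor a starting point for the follow-up period.

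Stopping study drug early is foreseen. Section 3.5 lists, among other reasons, "Serious adverse reactions require discontinuation of trial drug treatment".

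**The concern.** The endpoint and the scan that has to inform it run on different clocks. The endpoint counts from randomisation, the scan from the end of study drug. The clocks nearly agree for a patient who takes exactly 12 weeks of study drug, and they drift apart for anyone who stops early or finishes late.

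Stopping and delay happen after randomisation and may be related to treatment. If they differ between arms, one arm's month-6 status is read systematically earlier or later than the other's. An earlier last scan leaves more time for progression that no scheduled scan picks up before the landmark, which flatters the arm with more early stops. If stopping is the same in both arms, what suffers is mainly the accuracy of each arm's rate.

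**Working it through.** **Inputs**
- Landmark: 6 months from randomisation (section 4.1).
- Planned treatment: 4 × 21 = 84 days = 12 weeks (section 3.8). This agrees with Table 2's last treatment visit.
- First follow-up scan: 3 months after drug withdrawal; later scans every 3 months (Table 2).
- Conversion: 1 month = 365.25/12 = 30.44 days, so 3 months = 13.04 weeks and 6 months = 26.09 weeks.

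**Step 1: when the scans fall.** First follow-up scan = stop week + 13.04. Next scan = stop week + 26.09.

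| Study drug ends | First follow-up scan | Relative to month 6 | Next scan |
|---|---|---|---|
| Week 3 | week 16.0 (3.7 months) | 10.0 weeks before | week 29.1 (6.7 months) |
| Week 6 | week 19.0 (4.4 months) | 7.0 weeks before | week 32.1 (7.4 months) |
| Week 9 | week 22.0 (5.1 months) | 4.0 weeks before | week 35.1 (8.1 months) |
| Week 12, as planned | week 25.0 (5.8 months) | 1.0 week before | week 38.1 (8.8 months) |
| Week 15, after delays | week 28.0 (6.4 months) | 2.0 weeks after | week 41.1 (9.4 months) |

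These rows count follow-up from the actual stop date, as the column is labelled. Table 2 does not say whether an early stopper keeps the week-12 scan. Keeping it would not change the table, because every first follow-up scan listed falls after week 12.

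**Step 2: how much this could matter.** The documents give no stopping rates, so this step is an illustration. Assumptions:
- exponential PFS with the same true month-6 rate p in both arms;
- stopping unrelated to progression;
- progression dated to the scan that shows it.

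The proportion still event-free at scan week t is p^(t/26.09). The section 2.2 planning rates are 50% and 10%, and their midpoint is 30%.

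| p | Read at week 25.0 (completer) | Read at week 22.0 (stop week 9) | Read at week 19.0 (stop week 6) |
|---|---|---|---|
| 0.50 | 0.514 | 0.557 | 0.603 |
| 0.30 | 0.315 | 0.362 | 0.415 |
| 0.10 | 0.110 | 0.143 | 0.186 |

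Suppose 30% stop early in one arm and 10% in the other. The artificial difference is (0.30 − 0.10) × (early stopper's reading − completer's reading):
- Stops at week 6: 0.20 × 0.100 = 0.020 for p = 0.30; 0.20 × 0.089 = 0.018 for p = 0.50; 0.20 × 0.076 = 0.015 for p = 0.10.
- Stops at week 9: 0.20 × 0.047 = 0.009 for p = 0.30; 0.20 × 0.043 = 0.009 for p = 0.50; 0.20 × 0.033 = 0.007 for p = 0.10.
- Equal stopping: 0.

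That is roughly 1 to 2 percentage points. Two points in an arm of 28 is 0.020 × 28 = 0.56 of a patient. If every early stop came at week 3, the p = 0.30 figure would be 0.20 × (0.477 − 0.315) = 0.032.

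All these figures lean high. PFS includes death, which is known without a scan, so only the progression part can be missed. For late finishers the error could go either way, depending on whether the week-28 scan is taken as the month-6 reading.

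**The case against.** The strongest reply is that the follow-up column was written with the planned 12 weeks in mind. Twelve weeks plus 3 months is about month 6, so it may be meant as the landmark visit, and the handling of early stoppers and visit windows may sit in a fuller protocol or analysis plan. This stands in part. For on-schedule completers the mismatch is one week, and the early-stopper dates hold only if the label is followed literally. But a window rule only assigns scans that exist. It cannot supply a month-6 scan for someone scanned at weeks 19 and 32.

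Three stronger readings are tempting and not supported:
- **That section 4.3 and Table 2 contradict each other.** The six-weekly interval is listed separately from end of treatment and follow-up. Read as the on-treatment interval, it matches weeks 6 and 12 exactly. Read as continuing, it would give a scan at week 24, and the long interval would disappear. The sentence is unclear rather than plainly in conflict.
- **That the interval after week 12 is itself the defect, because PFS dates become imprecise.** Anchoring the scan to month 6 leaves 26 − 12 = 14 weeks between scans, so this change does not address date precision, and the point does not rest on it.
- **That a bias of about 2 points has been shown.** The 30% against 10% split is assumed. The trial is double-blind, and nothing in the documents shows that stopping differs by arm.

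**Conclusion.** The mismatch of anchors is real. As labelled, Table 2 lets the timing of the primary reading depend on a post-randomisation event. For stops between weeks 3 and 12 the first follow-up scan falls 10 to 1 weeks before month 6, and if treatment runs to week 15 it falls 2 weeks after.

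The likely effect on the comparison is modest: none with equal stopping and equal underlying PFS, and about 1 to 2 points under the assumed unequal stopping at weeks 9 to 6, against a planned 40-point difference (50% against 10%). A reader might infer that early stoppers who progress before month 6 will necessarily be counted as successes. The article shows no rule for dating progression found between visits, so that remains an assumption. The sample size is not affected. The change is worth making because it is cheap and removes the dependence altogether.

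**What to change.** 1. In Table 2, count all imaging visits from randomisation, whatever the study-drug status, so that early stoppers keep the week-6 and week-12 scans.
2. Relabel the imaging visit now placed 3 months after withdrawal as month 6 (week 26) from randomisation, with a stated window, and read the primary status from that scan.
3. In section 4.3, say whether the six-weekly interval applies only during treatment, so that the sentence agrees with Table 2.

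Cost: the visit moves by about one week for completers. Some early stoppers are scanned at a different time and may have one more scan by week 26 than if follow-up ran from their stop date. For a week-6 stopper, that means weeks 6, 12 and 26 instead of weeks 6 and 19. Section 2.3 describes recruitment as ongoing, so the schedule can still be amended for patients who have not reached this visit.
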